### Outcomes

Table 1 shows the timing of the administration of measures. Baseline data include foster parent background variables (e.g., age and education) and child variables (e.g., gestational drug/alcohol exposure, age at separation from biological parents, number of previous placements, length of the current placement, and significant mental/physical health problems). T1 is the baseline, T2 is 20 weeks post T1 baseline, and T3 is 6 months post T2.

**Table 1 Tab1:** Outcomes

	Measure	Child age	T1	T2	T3
*Foster Parent measures*					
Background variables for foster parent			√		
Well-being	WHO-5 index		**√**	√	√
Parental Stress	PSS		**√**	√	√
Parental Reflective Functioning	PRFQ		**√**	√	√
*Child measures*					
Background variables for foster children		4–17	**√**		
Child psychosocial adjustment (caregiver)	CBCL	4–17	**√**	√	√
Child psychosocial adjustment (self-report)	SDQ self-report	10–17	**√**	√	**√**
Child Well-being	KIDSCREEN 10-index	8–17	**√**	√	**√**
Child attachment	SSAP	4–9	**√**	√	
*Relationship measures*					
Parental Mind-mindedness	Describe your child procedure		**√**	**√**	
Child Mind-mindedness	Describe your friend procedure	10–17	**√**	**√**	
Coding interactive behavior (video)	CIB		**√**	**√**	
*Other outcomes*					
Placement breakdown	Administrative data			**√**	√

### Primary outcome

The Child Behavior Checklist (CBCL) measures psychosocial adjustment and is a component of the Achenbach System of Empirically Based Assessment (ASEBA) [51, 52]. The ASEBA is used to detect behavioral and emotional problems in children and adolescents. The CBCL consists of 113 questions, scored on a three-point Likert scale (0 = absent, 1 = occurs sometimes, 2 = occurs often). Foster parents for all children in the trial will complete the CBCL. The CBCL/6–18 (used with children 6 to 18 years old) consists of eight syndrome scales: (1) anxious/depressed, (2) depressed, (3) somatic complaints, (4) social problems, (5) thought problems, (6) attention problems, (7) rule-breaking behavior, and (8) aggressive behavior. The syndrome scales group into two higher-order factors: (1) internalizing and (2) externalizing. The timeframe for item responses is the past six months. The CBCL also includes competence scales for activities, social relations, school, and total competence. The CBCL is widely used and has proven to be a useful tool for detecting psychopathology in children and shows good results regarding both validity and reliability [53]. Danish norms are available for children throughout the age range of children within the trial [51, 52]. A low score on the Total Problem Scale is beneficial.

### Secondary outcomes

Kidscreen-10 is a ten-item parental and self-report measure of child well-being (health-related quality of health) [54]. Items are scored from 1 (never) to 5 (always) except for items 1 and 9 (reverse). Items 1 and 2 explore the level of the child’s/adolescent’s physical activity, energy, and fitness. Items 3 and 4 cover how much the child/adolescent experiences depressive moods and emotions, and stressful feelings. Items 5 and 6 ask about the child’s/adolescent’s opportunities to structure and enjoy their social and leisure time and participation in social activities. Item 7 explores the quality of the interaction between the child/adolescent and parent or caregiver and the child’s/adolescent’s feelings toward their parents/caregivers. Item 8 examines the nature of the child’s/adolescent’s relationships with other children/adolescents. Finally, items 9 and 10 explore the child’s/adolescent’s perception of their cognitive capacity and satisfaction with school performance. A higher score is better [54]. Kidscreen-10 is used as a self-report measure for children aged 10 or above, while the parental rating version is used within all families.

The Strengths and Difficulties Questionnaire (SDQ) [55, 56] for 11–17-year-old children is a 25-item measure of child behavior and psychopathology. Items are rated by the foster child on a three-point scale (not true, somewhat true, certainly true). The SDQ consists of five domains: hyperactivity/inattention, peer problems, conduct problems, emotional symptoms, and pro-social behaviors. The SDQ also has an additional seven-item impact supplement about daily function. Foster children from 10–17 years old will receive the SDQ. A high score indicates more problems.

The Parental Reflective Functioning Questionnaire (PRFQ) is an 18-item measure of parental reflective function or mentalization [57]. The PRFQ consists of three subscales. The first subscale: Pre-Mentalizing Modes (PRFQ-PM) contains 6 items (a low score indicates better function). The second subscale: Certainty about Mental States (PRFQ-CMS) contains 6 items (a high score indicate better function), and the third subscale: Interest and curiosity in mental states (PRFQ-IC) also contains 6 items (a high score indicate better function) [57]).

The Parental Stress Scale (PSS) [58, 59] is an 18-item measure of parental stress that is rated on a five-point scale (Strongly disagree, Disagree, Undecided, Agree, Strongly agree). Total score range is from 18 to 90, where a low score indicates less stress.

The WHO-5 index [60, 61] is a five-item questionnaire assessing the emotional well-being of foster parents. The WHO-5 index can also be used as a screening tool for symptoms of depression. It consists of five positively formulated items. The degree to which these feelings were present in the two weeks prior to completing each questionnaire will be scored on a 6-point Likert-type scale ranging from 0 (not present) to 5 (constantly present). Item scores are summated and transformed to a 0–100 scale, with lower scores indicating poorer well-being. The WHO-5 index has been cross-culturally validated and has proven to be psychometrically sound [60, 61].

Family functioning will be measured by six items inspired by the General Functioning subscale of the Family Assessment Device (FAD-GF). The FAD-GF assesses overall healthy functioning or dysfunction of intra-familial relationships. The six items were selected to reflect the domains included in the McMaster Model of Family Functioning: problem-solving, communication, roles, affective responsiveness, affective involvement, and behavioral control [62]. In order to make items comprehensible to younger children, some items were slightly rephrased. Higher scores indicate greater family dysfunction.

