### Statistical analysis

We will estimate the mean treatment effect of MBT relative to UC on the primary outcome (CBCL) as well as each of the secondary outcomes (Parental Well-Being, Stress, and Reflective Functioning, SDQ, Kidscreen, SSAP, and Parental Mind-Mindedness) at T2 and T3 separately, but using the same method each time, as follows.

Treatment assignment will be stratified into municipalities, and within each stratum, it will be assigned to clusters based on foster care consultants. Hence the estimation needs to account for both the stratification and the clustering. We will thus use linear regression for T2 and T3 outcomes separately, in each case controlling for pre-treatment outcomes. Within each stratum, we will then use linear regression, estimating robust clustering standard errors in order to account for the potential correlation between subjects assigned to the same consultant. Using the strata-specific treatment effects, we will then compute the mean treatment effect as the weighted mean of the within-stratum estimates weighted by stratum share. We can calculate the variance by averaging the within-stratum cluster robust variance, weighted by stratum share squared [70]. All analyses will use a significance level of 0.05.

Analyses will be based on the intention-to-treat (ITT) principle, analyzing each subject as part of the treatment to which they were originally assigned, regardless of whether treatment was in fact received.

If there is substantial attrition in outcome data collection, this will potentially introduce selection bias in the estimated effect if attrition selection is on unobservables. While doing so does not solve the problem of attrition selection on unobservables, we will follow the standard in the literature and analyze sensitivity by handling missing values using multiple imputation using all baseline variables.

Further, we will perform subgroup analysis in order to examine whether treatment effects differ across subgroups based on age (4–9 and10–17 years), number of previous foster care placements, municipality budget per capita (low or high) as well as parental background variables.

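### The stated Kidscreen-10 scoring rule leaves the depressive-mood and stress items (3 and 4) unreversed in a total where a higher score is better

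*Protocol article*

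**What the plan says.** The Kidscreen-10 paragraph under Secondary outcomes makes three statements that bear on direction.

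- The scoring rule: "Items are scored from 1 (never) to 5 (always) except for items 1 and 9 (reverse"). No other item is named as an exception.
- The content of two of the items not excepted: "Items 3 and 4 cover how much the child/adolescent experiences depressive moods and emotions, and stressful feelings".
- The direction of the total: "A higher score is better [54"].

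It introduces the other relevant pairs with "Items 1 and 2 explore the level of the" child's physical activity, energy and fitness, and "Finally, items 9 and 10 explore the" child's view of their own cognitive capacity and school performance.

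On who is measured, the same paragraph says "Kidscreen-10 is used as a self-report measure for children aged 10 or above", with the parent-rated version used in every family. Table 1 under Outcomes lists the "KIDSCREEN 10-index" for ages 8–17.

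The Statistical analysis section commits to estimating a treatment effect at T2 and at T3 on the primary outcome "as well as each of the secondary outcomes (Parental Well-Being, Stress, and Reflective Functioning, SDQ, Kidscreen, SSAP, and Parental Mind-Mindedness").

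**The concern.** A scoring rule has to point every item the same way as the total. Here two items that measure low mood and stress are scored upwards with frequency, in a total meant to rise with well-being. Improvement on those two items would lower the score and cancel part of any improvement on the others.

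Child well-being is named in the research aim and in the superiority hypothesis, and Kidscreen is tested at two time points. A score with mixed directions pulls a real benefit towards zero and makes the scale hard to interpret or to compare with other studies. The Table 1 age range adds a smaller inconsistency about which children contribute data.

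**Working it through.** The plan gives no figure to reproduce on this point. The check applies the stated rule to the item content in the same paragraph.

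**Inputs from the article.** There are ten items, each scored 1 to 5. Items 1 and 9 are reversed. Items 3 and 4 are worse when more frequent. A higher total is better.

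**Assumptions, not in the article.** The total is an unweighted sum. A reversed item scores 6 − x. Correctly keyed items have equal variance, equal treatment effects and a common inter-item correlation ρ, shown from 0.1 to 0.5.

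**Step 1: score range.** Take the reading kindest to the text, in which items 1 and 9 are negatively worded and so rightly reversed. Only items 3 and 4 then point the wrong way.

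- Best possible child: 8 × 5 + 2 × 1 = 42.
- Worst possible child: 8 × 1 + 2 × 5 = 18.
- Spread: 42 − 18 = 24.
- Spread with all ten items aligned: 50 − 10 = 40.
- Ratio: 24 / 40 = 60%.

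With equal item effects a raw group difference shrinks by the same factor: eight items add, two subtract, and the net weight is 6 of 10.

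**Step 2: standardised effect.** Let S be the net sum of item signs. With unit item variance and an effect δ on each item, the mean difference in the total is δS and its variance is 10 + ρ(S² − 10). Hence d = δS / √(10 + ρ(S² − 10)). With S = 6 the denominator is √(10 + 26ρ). With S = 10 it is √(10 + 90ρ). The ratio of the as-written effect to the correctly keyed effect does not depend on δ:

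| ρ | As written, 6/√(10 + 26ρ) | Correct, 10/√(10 + 90ρ) | Ratio |
|---|---|---|---|
| 0.1 | 6/√12.6 = 1.690 | 10/√19 = 2.294 | 0.74 |
| 0.3 | 6/√17.8 = 1.422 | 10/√37 = 1.644 | 0.87 |
| 0.5 | 6/√23 = 1.251 | 10/√55 = 1.348 | 0.93 |

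**Step 3: items 1 and 9.** Both belong to pairs described by positive content, and in each pair only one item is reversed: item 1 but not item 2, item 9 but not item 10. That pattern would be right if items 1 and 9 were worded negatively or had a different response format, and wrong if they were worded like their partners. The article gives no item wording, so the check stops there.

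**Step 4: age range.** The Participants section admits target children aged 4–17. Self-report starts at age 10 under Secondary outcomes, and the Data collection section sends child questionnaires to those aged 10 and older, so self-report covers 10–17. The parent version goes to all families, so it covers 4–17. The 8–17 in Table 1 matches neither.

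**The case against.** The strongest reply is that this is a loose sentence in a condensed article. Kidscreen-10 is an existing instrument, the article cites a source for the direction of its score, and the trial team may well score it from the published key. That reply stands as a limit on the consequence: if the instrument's key is used, the fault is one of description and no result changes. It does not remove the contradiction, because the article chose to state the list of reversed items and nothing elsewhere in it corrects that list.

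A reader might go further and infer that items 1, 3, 4 and 9 are all miskeyed. Then S = 2, the range runs from 26 to 34, and at ρ = 0.3 the standardised effect falls to 2/√8.2 = 0.698 against 1.644, a ratio of 0.425 or a loss of about 57%. The document does not support that as a finding. The paragraph describes what the items are about, not how they are worded, and a negatively worded item on energy or attention would be rightly reversed.

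A reader might also infer that the plan fails to say whose Kidscreen rating is analysed. Who completes which version is settled by the Secondary outcomes and Data collection sections. Which version enters the analysis may be left to a statistical analysis plan that is not shown. Only the table cell is inconsistent.

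**Conclusion.** The point holds for items 3 and 4 and follows from one paragraph of the article. If data were scored from that paragraph with only these two items miskeyed, raw differences on child well-being would be 60% of their proper size. Standardised effects would be about 0.74 to 0.93 of their proper value, a loss of roughly 7% to 26%. These figures rest on the assumptions listed in the check; the correlation range is illustrative and not taken from the article.

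The keying of items 1 and 9 is doubtful but undetermined. The Table 1 age range is a separate small error.

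The consequence is confined to one secondary outcome at T2 and T3. The CBCL primary outcome is unaffected, and so is the sample size, which the Power considerations section bases on overall psychosocial adjustment.

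**What to change.** Correct the scoring sentence so that items 3 and 4 are reversed. Check the keying of items 1 and 9 against the instrument manual, and keep or remove their reversal accordingly. Check the scoring code against the same manual before any Kidscreen data are analysed. Correct the age entry in Table 1 so that it shows 10–17 for self-report and 4–17 for the parent version, as the text describes.

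The cost is one sentence, one table cell and a review of the scoring code. No new data are needed, and item-level responses already collected can be rescored.

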#### Parent–child relationship

Coding Interactive Behavior (CIB) [63] is a global video-based coding system that assesses the foster parent–child relationship. The CIB includes 44 rating scales coded from 1 (a little) to 5 (a lot); 21 are parent codes, 16 are child codes, five are dyadic codes, and two are overall codes, which aggregate into the following higher-order composites: maternal sensitivity, maternal intrusiveness, child social engagement, and dyadic reciprocity. The system has versions for newborns, infants and toddlers, preschoolers, and adolescents. The CIB is coded based on a six-minute video recording of free play or interaction between parent and child in the home. The CIB system has been validated as an assessment measure in multiple studies of mother–child interactions in both normative and high-risk populations. It shows stability over time, predictive validity, and adequate psychometric properties [63]. In the present trial, the video coding of CIB will be based on a video of the child and the primary foster parent. Interactions will be coded by reliable coders blind to treatment allocation. The inter-coder agreement will be calculated on a 10% randomly selected subset of the sample.

#### Child attachment

The Story Stem Assessment Profile (SSAP) is a narrative-based measure to assess internal representations in 4-to-11-year-old children [25, 64]. Using a standard doll family and play materials, the interviewer enacts the beginning of a story (a story stem) and asks the child to complete the story using the provided play materials. The method allows the child to enact the story in a playful manner creating a narrative based on both verbal and non-verbal inputs, offering a unique insight into the child’s perception of the nature and quality of relationships. The SSAP entails a set of 13 story stems, which introduce the beginning of a story for the child to complete, within which lies "an inherent dilemma". It "allows an assessment of the child's expectations and perceptions of family roles without asking the child direct questions about their own family, which might cause the child undue conflict or anxiety. A shortened version of the SSAP consisting of seven stories, which has demonstrated robust psychometric properties and has been validated with looked-after children in the UK, will be used in the trial [25, 64]. Attachment will be coded by reliable coders blind to treatment allocation. The inter-coder agreement will be calculated on a 10% randomly selected subset of the sample.

#### Parental mind-mindedness

Parental mind-mindedness refers to a caregiver’s attunement to their children’s mental and emotional states [65]. In infancy, mind-mindedness is assessed from caregivers’ tendency to comment appropriately on their infants’ thoughts or feelings or from caregivers’ meaningful interpretations of their infants’ early non-word vocalizations [66]. In children beyond infancy, mind-mindedness is assessed in terms of parents’ tendency to spontaneously focus on mental characteristics when given an open-ended invitation to describe their child. In the present study, foster parents will be asked to complete the describe-your-child measure online [67], and coding will be carried out as described in previous studies with children in foster care [66]. Mind-mindedness will be coded by reliable coders blind to treatment allocation. The inter-coder agreement will be calculated on a 10% randomly selected subset of the sample.

#### Child mind-mindedness

Child mind-mindedness refers to children's tendency to adopt an intentional stance in their interactions with and representations of others, measured as their proclivity to use mentalistic descriptors in their representation of others [68, 69]. Mentalistic descriptors refer to any references to mental life and intellect (e.g., 'she is always thinking about him', 'he is a clever person'). References to likes and dislikes are only included if they do not focus exclusively on the friend's behavior (e.g., 'she likes blue' and 'she doesn't like her brother or her sister using her stuff’ are coded as mentalistic, but ‘she likes playing football’ is coded as behavioral). Also included in mentalistic descriptors are references to the friend's responses to the child's emotions (e.g., 'she plays with me when I'm feeling sad'), and to the friend's own emotions, but not their external manifestations (e.g., 'she's always really happy', but not 'always smiling'. In the present study, foster children aged 10 or above will be asked to complete the describe-your-friend measure online, and coding will be carried out as described in the manual [68, 69]. Mind-mindedness will be coded by reliable coders blind to treatment allocation. The inter-coder agreement will be calculated on a 10% randomly selected subset of the sample.

### Blinding

As the participants will be offered extra support in the intervention group, neither participants nor foster care consultants can be blinded. Data analysts, video coders, and data assessors will be blind to allocation status.

### Power considerations

Based on previous research, we expect an effect size of *d* = 0.53 for children’s overall psychosocial adjustment [40]. Based on 23 foster care consultants in each group, a power of 0.80, a type 1 error rate of 0.05, and an intra-class correlation (ICC) of 0.1, we need to include 3 families for each foster care consultant in the study (a total of 138 families). We aim to recruit 175 families (3.8 for each foster care consultant) to leave room for drop-out and allow power to conduct moderator analyses.

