## Discussion

This prospective cluster-randomized controlled trial aims to explore the effects of MBT for foster families and foster children aged 4–17 years old in Denmark on measures of child mental health and well-being, foster/parent–child relationship and attachment, as well as foster parent stress and mental health. Furthermore, follow-up measures included in the trial may enable analyses of the effectiveness of the MBT intervention in preventing placement breakdown, which is a known risk factor for long-term positive outcomes for children in foster care. To our knowledge, this is the first randomized controlled study examining the effects of an attachment-based intervention on foster families in the Scandinavian context. This is paradoxical, as the importance of attachment theory within foster care is often seen as taken-for-granted knowledge in official documents and clinical guidelines [17].

In Denmark, there are rather large differences between the municipalities in terms of sociodemography and population size, which results in large differences regarding the number of children placed in care within each municipality. This means that municipalities with relatively many children in care also have a high number of highly skilled foster care consultants, or they may already have psychologists or family therapists who provide therapeutic interventions for foster families in times of high stress. On the other hand, some municipalities with more budgetary restrictions or with very few children in care may only employ a few foster care consultants. Consequently, the practical execution of the study will be streamlined as much as possible but with a high degree of respect for what is actually possible within the participating.

The MBT therapists who receive the training will vary in terms of educational background and clinical experience. This is likely to cause variation in the delivery and receipt of the MBT intervention. The study will provide insight into these differences, as we will be able to conduct moderator analysis based on therapist characteristics.

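### The protocol's own sizing inputs do not support the statement that 175 families give power for moderator analyses

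*Protocol article*

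**What the plan says.** The Power considerations section of the protocol article states the expected main effect: "we expect an effect size of *d* = 0.53 for children’s overall psychosocial adjustment". The other inputs are 46 consultants split equally between the arms, 80% power, a 5% significance level and an ICC of 0.1. From these it derives 3 families per consultant, 138 in all. It then sets a target of 175 (3.8 per consultant), with the reason "to leave room for drop-out and allow power to conduct moderator analyses". No drop-out rate, interaction size, subgroup split or power level is attached to that reason.

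The Statistical analysis section says that "we will perform subgroup analysis in order to examine whether treatment effects differ across subgroups". It names age (4–9 against 10–17), number of previous placements, municipality budget (low or high) and parental background. It also says "All analyses will use a significance level of 0.05" and plans to control for the pre-treatment outcome. The Discussion adds that "we will be able to conduct moderator analysis based on therapist characteristics".

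**The concern.** The 37 families between 138 and 175 are asked to do two jobs, and neither is quantified. An interaction contrast between two equal subgroups has about four times the variance of the main-effect contrast (somewhat less when the moderator varies within consultants). A trial sized for 80% power on the main effect is therefore normally far from powered for effect modification, and a 27% larger sample (175/138 = 1.27) does not close that gap.

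What is at stake is interpretation. Several moderators are to be tested at 0.05. If the published plan says that the trial has power for them, a reader could take a non-significant age or municipality interaction as evidence of a uniform effect, or give a chance positive more credit than it deserves.

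**Working it through.** **Inputs from the protocol.** d = 0.53 in SD units; 23 consultants per arm; ICC 0.1; alpha 0.05; 138 and 175 families. Sidedness is not stated. Two-sided is assumed, because it reproduces the protocol's figure. The sizing uses no baseline adjustment.

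**Step 1: reproduce 138.** With m = 3 families per consultant, the design effect is 1 + (3 − 1) × 0.1 = 1.2. The main-effect SE is √(4 × 1.2 / 138) = 0.1865. Power is Φ(0.53/0.1865 − 1.96) = Φ(0.88) = 81% (79% with a t reference on 44 df). Two families per consultant would give 68%, so 3 is the smallest whole number and 138 is confirmed. With all 175 analysed, main-effect power is 87%.

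**Step 2: the margin.** 1 − 138/175 = 21.1%. Drop-out of that size would return the trial to 138 families. This rate is solved from the two sample sizes; the protocol does not state it.

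**Step 3: interaction, unadjusted, equal subgroups.** SE = √(4v / (N × ½ × ½)) = √(16v/N).
- Moderator varying within consultants: v = 1 − ICC = 0.9.
- Moderator fixed by consultant or municipality: v = the full design effect, 1.28 at 3.8 families per consultant and 1.2 at 3.

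Power is Φ(interaction/SE − 1.96). The interaction detectable with 80% power is 2.802 × SE.

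| Families analysed | Moderator | SE | Power for 0.53 | Power for 0.265 | Detectable at 80% |
|---|---|---|---|---|---|
| 175 | within consultants | 0.287 | 46% | 15% | 0.80 SD |
| 175 | consultant or municipality | 0.342 | 34% | 12% | 0.96 SD |
| 138 | within consultants | 0.323 | 38% | – | about 0.91 SD |
| 138 | consultant or municipality | 0.373 | 30% | – | about 1.05 SD |

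Equal subgroups are the best case. At 175 families, power for 0.53 falls to about 30–40% with a 30:70 split and 24–31% with 20:80. A t reference lowers the figures by a further 1 to 2 points. The municipality row uses only the consultant design effect. With 10 municipalities, any variation of the effect between them would lower it further.

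**Step 4: baseline adjustment.** The protocol gives no baseline correlation, so r is an assumption. The SE is multiplied by √(1 − r²). With 175 analysed and equal subgroups:

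| Assumed r | Power for 0.53: within / cluster-level | Power for 0.265: within / cluster-level |
|---|---|---|
| 0.5 | 57% / 43% | 19% / 14% |
| 0.6 | 64% / 49% | 21% / 16% |
| 0.7 | 74% / 58% | 25% / 19% |
| 0.8 | 87% / 73% | 34% / 25% |

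**The case against.** The strongest reply is that the planned analysis is adjusted, so a reader who infers that 34–46% is the ceiling for this trial goes too far. That stands. At an assumed r of 0.8 a within-consultant moderator passes 80% power for an interaction of 0.53. This needs a high correlation, no drop-out, equal subgroups and an interaction as large as the main effect, all at once. A moderator fixed by consultant or municipality does not reach 80% even then.

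A second reply is that drop-out need not consume the margin. This also stands: no rate is stated, and 21% exhausts the margin by construction. With less drop-out some families remain. The 138 is itself unadjusted. At r = 0.6, 2 families per consultant (92 in all) would give an SE of 0.8 × √(4 × 1.1/92) = 0.175 and about 86% main-effect power. It cannot be said that nothing is left for moderators, only that what is left falls short on the protocol's own inputs.

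Third, the protocol attaches no power level to the moderator clause, and no printed figure is miscalculated. The fault is an unsupported statement. An article may leave moderator assumptions to a fuller document, but this one asserts the property and its own figures point the other way.

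Fourth, the Discussion sentence on therapist characteristics might be read as another power claim. It says only that the analysis will be possible. Nor does any passage say that a null interaction will be reported as no difference; that risk is a reader's inference, not a stated plan.

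**Conclusion.** The point holds as a conditional one. On the same unadjusted inputs that reproduce the 138, recruiting 175 families does not give useful power for moderator analyses. Even with full follow-up and equal subgroups, an interaction equal to the whole main effect would be missed more often than found. For a more modest interaction of half that size, the conclusion does not depend on the unknown baseline correlation over the range tried, up to 0.8. The figures rest on two-sided 0.05, a normal approximation and equal subgroups, and the adjusted figures also on an assumed correlation. The main-effect sample size is sound and is not in question.

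**What to change.** In Power considerations, delete the part of the sentence that claims power for moderator analyses. State instead that 175 families allow for up to about 21% drop-out while keeping about 80% power for the main effect, and that subgroup and moderator analyses are exploratory and not powered. Give the smallest interaction detectable with 80% power, unadjusted and with equal subgroups: about 0.80–0.96 SD with 175 families analysed and about 0.91–1.05 SD with 138. The two ranges should stay tied to their sample sizes; 0.80 SD must not be paired with 21% drop-out. If the sponsor prefers to keep a power statement, it should give the assumed drop-out, interaction size, subgroup share and baseline correlation behind it.

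For each moderator that exists in both arms, report the arm-by-moderator interaction with its 95% confidence interval, and do not read a non-significant interaction as evidence of no difference. Characteristics recorded only for the MBT therapists (23 consultants) have no such interaction; present them as descriptive associations within the MBT arm. Mark the Discussion sentence as exploratory.

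The power text is a wording change that makes a stated property less favourable. The reporting rule needs a line in the analysis plan. The planned analysis fits regressions within each municipality and averages them, so moving to one pooled interaction model would be an analysis change to prespecify, not an edit of wording. Recruitment, sample size and the primary analysis stay as they are.
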